### Sample Size Determination and Power Analysis

Sample size determination was based on power analysis of several biomechanical, subjective, and functional measures collected during pilot investigations (Table 2). Assuming an α error rate of 5% and using within-group SDs determined from the pilot investigations, power is provided for selected parameters for a sample size of 100 participants for functional and subjective outcomes and a sample size of 30 for biomechanical parameters.

**Table 2 table2:** Sample size determination and power analysis of selected parameters.

Parameters		Difference, mean (SD)	Power (N=100; subset of 30/100, 30%, where appropriate), %

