**Methods:**

This investigation will be a multisite, randomized, crossover clinical trial targeting the enrollment of 100 participants. Participants will use 3 different types of prosthetic devices (energy storing and returning, articulating, and powered) in random order. Participants will be fitted and trained with each device and then separately use each device for a 1-week acclimation period. Following each 1-week acclimation period, participants will be evaluated using several functional measures and subjective surveys. A random subset of participants (30/100, 30%) will also undergo full-body gait analysis, following each 1-week acclimation period, to collect biomechanical data during level ground and incline and decline walking. After all individual device evaluations, participants will be given all 3 prostheses concurrently for 4 weeks of home and community use to capture user preference. Activity monitoring and a guided interview will be used to determine overall user preference.

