#### Biomechanical Analysis

In addition to completing the functional and subjective outcome measures during visits 3 to 5, a subset of 30% (30/100) of the participants will also undergo gait analysis during these visits. Biomechanical gait analysis will include kinetic and kinematic evaluation of level ground walking at 3 speeds and kinematic evaluation of incline and decline ambulation at a self-selected speed. The purpose of these sessions is to collect joint angles, forces, torques, and powers while participants use each ankle-foot device.

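### The five functional and subjective powers in Table 2 are labelled N=100 but are about n=30 figures with no gain from pairing, and two biomechanical rows do not reproduce

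*Protocol article*

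**What the plan says.** The Abstract describes the design: "This investigation will be a multisite, randomized, crossover clinical trial targeting the enrollment of 100 participants". Each participant uses all three device types, so device comparisons are within person.

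Under Sample Size Determination and Power Analysis, the basis of the calculation is "Assuming an α error rate of 5% and using within-group SDs determined from the pilot investigations". The section then states that "power is provided for selected parameters for a sample size of 100 participants for functional and subjective outcomes". For the gait measures it gives a smaller number: "a sample size of 30 for biomechanical parameters". The power column of Table 2 repeats this: "Power (N=100; subset of 30/100, 30%, where appropriate".

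The smaller number belongs to gait analysis only. The Biomechanical Analysis section says that "a subset of 30% (30/100) of the participants will also undergo gait analysis during these visits". The functional and survey battery at Visits 3 to 5 and the step monitoring at Visit 6 are not limited to that subset.

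Neither the test nor its sidedness is named, and no within-person correlation is given. The table prints each SD beside a mean difference, while the text calls the SDs within-group.

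**The concern.** PEQ frustration is entered as a difference of 15.9 with SD 24.7, or 0.64 SD. A within-person comparison of 100 people should detect that almost always, yet the table gives 68.6%. Steps at high activity (9, SD 13.1, or 0.69 SD) is given 74.4%. Both look far too low for the stated sample size.

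This table is the article's only stated basis for choosing 100 and 30. The trial also aims to find which measures respond to device type, so a reader will use the table to judge how small a difference each measure could show. Powers belonging to another sample size mislead on that.

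**Working it through.** **Inputs.** Differences, SDs and stated powers are from Table 2; alpha 5%, N=100 and n=30 are from the text above it. Assumptions: two-sided tests, and within-person correlation rho, varied because it is not given.

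**Formulas** (noncentral t, d = difference / SD):
- Unpaired, n per group: noncentrality = d × √(n/2), df = 2n − 2.
- Paired, n participants, within-group SD: SD of differences = SD × √(2(1 − rho)), noncentrality = difference × √n / SD of differences, df = n − 1. At rho = 0 the noncentrality is again d × √(n/2).

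**Step 1: the plan's own figures.** Example, PEQ frustration: d = 15.9/24.7 = 0.644. Unpaired with 30 per group: 0.644 × √15 = 2.49, df 58, power 68.85%. Paired with N=100 and rho = 0: 0.644 × √50 = 4.55, df 99, power 99.46%.

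| Row | Stated % | Unpaired, 30 per group | Paired, n=30, rho=0 | Paired, N=100, rho=0 | Paired, N=100, rho=−1 |
|---|---|---|---|---|---|
| PEQ satisfaction | 98.7 | 98.67 | 98.4 | 100.0 | 99.97 |
| PEQ frustration | 68.6 | 68.85 | 67.4 | 99.46 | 89.0 |
| PEQ utility | 95.5 | 95.30 | 94.7 | 100.0 | 99.7 |
| Steps at high activity | 74.4 | 74.43 | 73.0 | 99.78 | 92.5 |
| 6-minute walk | 96.3 | 96.29 | 95.7 | 100.0 | 99.8 |

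Solving the unpaired test for n gives 30.1, 29.8, 30.3, 30.0 and 30.0 per group.

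**Step 2: does rounding of the inputs explain the gaps?** Moving each difference and SD by half a unit in its last printed digit, the unpaired test spans 98.55 to 98.77, 68.41 to 69.30, 94.88 to 95.71, 69.2 to 79.2 and 95.77 to 96.77%. All five stated values lie inside.

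**Step 3: can any N=100 reading give the table?** Power falls as rho falls, and rho = −1 is the mathematical floor. Even there every row exceeds its stated value. Treating the tabled SD as the SD of differences gives at least 99.99% on all five rows. Unpaired with 100 per group gives 99.5% (frustration) and 99.8% (high activity); with 50 per group, 89.0% and 92.5%. Nothing at N=100 fits the five as a set.

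**Step 4: multiplicity.** At Bonferroni alpha .05/3 = .0167, N=100 and rho = 0, the lowest rows are 98.2% (frustration) and 99.2% (high activity).

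**Step 5: two biomechanical rows, correctly labelled n=30.**
- Effective foot length ratio: 0.9/0.06 = 15 SDs, so power is 100%. The stated 99.2% needs d of about 1.15 (unpaired).
- Radius of curvature: 7.3/9.2 = 0.793. Power is 85.6% unpaired with 30 per group, 84.4% paired with rho = 0, and 98.7% if 9.2 is the SD of differences. None gives 81.7%.

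**Step 6: 6-minute walk difference detectable at 80% power, N=100.** The detectable difference is 0.283 SDs of differences at alpha .05 and 0.328 at .0167.
- If 61 m is the SD of differences: 0.283 × 61 ≈ 17 m, or 0.328 × 61 ≈ 20 m.
- If 61 m is a within-group SD and rho = 0, SD of differences = 61 × √2 = 86.3 m: ≈ 24 m, or ≈ 28 m.

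**The case against.** The strongest reply is that the error is harmless. It understates power, no analysis or decision rule in the Statistical Analysis section uses Table 2, and the sample size stands. That is right, and it makes this a reporting correction rather than a design fault. It does not make the printed figures correct.

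Several stronger readings are tempting and should not be drawn:
- *That a parallel-group calculation was used.* The article names no test. The unpaired test with 30 per group is the best fit, but a paired test with 30 participants and zero correlation comes within 1.5 points on every row. The firm statement is n of about 30 with nothing gained from pairing.
- *That a null result could not be interpreted.* It would be read from its estimate and interval, not from a planning table.
- *That the trial resolves 17 to 20 m on the walk test.* This takes 61 m as the SD of differences, whereas the text says "using within-group SDs determined from the pilot investigations". The range has to include 24 to 28 m.
- *That high-activity steps has 99.8% power in practice.* Step monitoring is described for the home phase, when participants choose freely among the three devices, so 100 complete pairs cannot be presumed. Every N=100 figure here also assumes no loss, although the article allows unenrolment.

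The foot length entry may be a single mistyped figure: a difference near 0.07 gives 99.2 to 99.4% at n=30. It still needs correcting. The unadjusted alpha is openly stated, and by Step 4 adjustment changes little for the N=100 rows; it is not part of the fault.

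**Conclusion.** The point holds in this form. Five powers attributed to 100 participants belong to about 30 without benefit from pairing. For 100 participants compared within person, at zero or positive correlation and without loss, the apparent shortfalls disappear: 68.6% becomes about 99.5%, and 74.4% becomes about 99.8%, the latter conditional on complete step data for each device. The other three rows are about 100%. The contradiction with the table does not depend on the correlation, because even rho = −1 gives more than the stated power on every row.

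The foot length entry is impossible as printed. Radius of curvature is 2.7 to 3.9 points below its recomputed value without pairing gain (84.4 − 81.7 and 85.6 − 81.7), more than input rounding explains. These two rows are separate faults and are not evidence about the N=100 label.

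**What to change.** - Recompute Table 2 as within-participant comparisons, with N=100 for functional and subjective outcomes and n=30 for biomechanical ones. Use the pilot SD of within-participant differences; if only within-group SDs exist, show power over a stated range of correlations. Name the test, its sidedness and alpha.
- For steps at high activity, state how many participants are expected to give usable data on each device and compute power for that number.
- Correct the effective foot length entry against the pilot data, and recheck radius of curvature.
- Optionally, add the difference detectable at 80% power, with its SD convention (for the walk test, the figures in Step 6).

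The cost is a recalculation from existing pilot data and a corrected table. Sample size, design and analyses are unchanged.

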**Subjective outcome measures**			
	PEQ^a^—satisfaction	13.6 (12.4)	98.7
	PEQ—frustration	15.9 (24.7)	68.6
	PEQ—utility	8.4 (8.8)	95.5

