**Functional outcome measures**			
	Steps at high activity (%)	9 (13.1)	74.4
	6-minute walk distance (m)	60 (61)	96.3

^a^PEQ: Prosthesis Evaluation Questionnaire.

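### The functional and subjective powers in Table 2 are labelled N=100, but the printed inputs give them for about 30 participants, so power at N=100 is understated

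*Protocol article*

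**What the plan says.** The abstract describes the design: "This investigation will be a multisite, randomized, crossover clinical trial targeting the enrollment of 100 participants". Each participant is tested with all three device categories, so device comparisons are within person.

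Under Sample Size Determination and Power Analysis, the article gives its inputs as follows: "Assuming an α error rate of 5% and using within-group SDs determined from the pilot investigations". It then says that "power is provided for selected parameters for a sample size of 100 participants for functional and subjective outcomes", with "a sample size of 30 for biomechanical parameters". The column heading of Table 2 repeats this: "Power (N=100; subset of 30/100, 30%, where appropriate".

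The five rows that carry the N=100 label are PEQ satisfaction, "PEQ—frustration", PEQ utility, "Steps at high activity" and 6-minute walk distance. The article does not say which test the powers refer to, whether it is two-sided, or what within-person correlation was assumed.

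**The concern.** This table is the only numerical support that the article gives for enrolling 100 people. A reader can check it, because differences, SDs, alpha and N are all printed. Two of the powers look too low at first sight: standardised differences of 0.64 and 0.69 with 100 people in a crossover should give power close to 100%, yet the table shows 68.6% and 74.4%.

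What is at stake is how results will be read. The study sets out to find which measures are sensitive to device type. If PEQ frustration or steps at high activity shows no difference, a reader of Table 2 would put that down to low power. At N=100, and with the pilot inputs, that explanation would be wrong.

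**Working it through.** **Inputs.** Alpha is 0.05, from the text and taken as two-sided. Differences and SDs are from Table 2. The SD is first read as within-group, as the text says: "using within-group SDs determined from the pilot investigations".

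**Formulas** (noncentral t, with d = difference/SD):

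- Two-sample, n per group: noncentrality d × √(n/2), with 2n − 2 degrees of freedom.
- Paired, n participants, within-person correlation ρ: SD of the difference = SD × √(2(1 − ρ)); noncentrality d × √n / √(2(1 − ρ)), with n − 1 degrees of freedom.

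Example for PEQ frustration: d = 15.9/24.7 = 0.644. With 30 per group the noncentrality is 0.644 × √15 = 2.49, which gives 68.9%. With 100 paired at ρ = 0 it is 0.644 × √50 = 4.55, which gives 99.5%.

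**Reproducing the printed figures, then computing at N=100** (power, %):

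| Row | Difference (SD) | Printed | Two-sample, 30 per group | Paired, 30, ρ=0 | Paired, 31, ρ=0 | Paired, 100, ρ=0 |
|---|---|---|---|---|---|---|
| PEQ satisfaction | 13.6 (12.4) | 98.7 | 98.7 | 98.4 | 98.7 | >99.9 |
| PEQ frustration | 15.9 (24.7) | 68.6 | 68.9 | 67.4 | 68.9 | 99.5 |
| PEQ utility | 8.4 (8.8) | 95.5 | 95.3 | 94.7 | 95.3 | >99.9 |
| Steps at high activity | 9 (13.1) | 74.4 | 74.4 | 73.0 | 74.5 | 99.8 |
| 6-minute walk | 60 (61) | 96.3 | 96.3 | 95.7 | 96.3 | >99.9 |

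Solving each row separately for the two-sample size that best matches the printed power gives 30 per group in all five rows.

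**Input rounding.** With 30 per group, the powers compatible with rounding are 98.6–98.8, 68.4–69.3, 94.9–95.7, 69.2–79.2 and 95.8–96.8. The steps range is wide because its difference is printed as a whole number (9), so that row discriminates less than the others. All five printed values lie inside their ranges.

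**Can any reading of N=100 give 68.6% and 74.4%?** Powers below are for PEQ frustration and steps, in that order.

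- Printed SD taken as the SD of the difference, paired, N=100: both over 99.9%.
- Paired, N=100, ρ=0, alpha divided by 3 for three device pairs: 98.2% and 99.2%.
- The 100 split into two groups of 50: 89.0% and 92.5%.
- Paired, N=100, with ρ at its mathematical limit of −1: again 89.0% and 92.5%.

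None comes near the printed values. If the SD is taken as that of the difference, the printed powers match a paired test on 16 or 17 people, which is further still from 100.

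**Detectable difference at N=100** (80% power, two-sided 0.05, paired; ρ = 0.5 to ρ = 0): 6-minute walk 17–24 m; PEQ frustration 7.0–9.9; PEQ utility 2.5–3.5; PEQ satisfaction 3.5–5.0; steps at high activity 3.7–5.2 percentage points. The correlations are assumptions, since the article gives none.

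**The case against.** The strongest objection concerns how far the fit can be pushed. A reader might infer from the two-sample match that the sponsor treated the devices as separate groups of 30 and ignored the crossover. The documents do not support that as a fact. No test is named, and a paired calculation on 31 people at zero correlation fits equally well. The gait rows lean slightly towards the paired version: for ankle range of motion (printed 95.3) paired n=30 gives 95.1 and two-sample 95.7; for peak plantarflexion (printed 91.1) they give 91.4 and 92.3. Neither version reproduces the radius-of-curvature row (printed 81.7; 84.4 and 85.6), so no single formula is shown to underlie the whole table. The column heading also leaves open whether the SD is that of the difference. All of this stands, and the point is therefore limited to the sample size, not the test.

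A second objection is that the error is harmless. It understates power, and three of the five rows (98.7, 95.5 and 96.3% against over 99.9%) lead to the same conclusion either way. This also stands: only PEQ frustration and steps at high activity change in meaning.

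A third concerns the number 100 itself. With these inputs all five rows reach 80% with 40 participants at zero correlation, and a reader might infer that 100 is too many. That does not follow. PEQ frustration only just gets there (80.2%), before any correction for pairwise comparisons or any loss of participants who do not reach the minimum performance standard. The planned covariate-adjusted mixed models and the logistic models of preference also make demands that pairwise power does not cover. Nor does the article claim that 100 is the minimum.

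None of these objections produces 68.6% or 74.4% at N=100.

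**Conclusion.** The point holds as a labelling or calculation error in the power table. The five functional and subjective powers are those of about 30 participants, not the stated 100. At N=100 the printed inputs give about 99.5% for PEQ frustration and 99.8% for steps, which are 30.9 and 25.4 points above the printed values (99.5 − 68.6 and 99.8 − 74.4), and over 99.9% for the other three.

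These figures assume a two-sided 5% level, within-group SDs, zero within-person correlation and data from all 100 participants. Positive correlation would raise them. That the printed powers are not for 100 does not depend on the correlation: even the extreme negative case leaves 89.0% and 92.5%. That they correspond to 30 does depend on reading the SDs as within-group, as the text says.

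The error is conservative. It does not show that the trial is underpowered, and it gives no reason to alter enrolment. It does mean that the table as printed does not describe N=100, and that two outcomes are wrongly shown below 80%.

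**What to change.** Recompute the functional and subjective rows of Table 2 for within-person device contrasts at N=100, and the gait rows for the same contrasts at N=30. Name the test and its sidedness, and say whether the SD is within-group or that of the within-person difference. If it is within-group, give the assumed correlation, for example 0, 0.5 and 0.7. Replace 68.6% and 74.4%, and add the detectable difference at N=100 for each row. If the table is not recomputed, the minimum is to relabel the functional and subjective figures as n=30.

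The cost is a recalculation and a corrected table. No additional participants, visits or changes to the analysis are needed.

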**Biomechanical parameters**			
	Ankle range of motion (°)	2.9 (3)	95.3
	Ankle peak plantarflexion (°)	3.2 (3.6)	91.1
	Peak ankle power (W/kg)	1.7 (0.7)	99.9
	Effective foot length ratio	0.9 (0.06)	99.2
	Instantaneous radius of curvature (cm)	7.3 (9.2)	81.7
**Subjective outcome measures**			
	PEQ^a^—satisfaction	13.6 (12.4)	98.7
	PEQ—frustration	15.9 (24.7)	68.6
	PEQ—utility	8.4 (8.8)	95.5
**Functional outcome measures**			
	Steps at high activity (%)	9 (13.1)	74.4
	6-minute walk distance (m)	60 (61)	96.3

^a^PEQ: Prosthesis Evaluation Questionnaire.

## Results

The study was funded in August 2017, and data collection began in 2018. Data collection is expected to be completed before July 2023. Data analysis of the full data set is expected to begin after final data collection. Initial dissemination of results is expected in the winter of 2023, with subsequent publication of secondary analyses in 2024.

## Discussion

### Expected Outcomes and Anticipated Principal Findings

The expected outcomes of this investigation are to generate data that offer new knowledge that can be used to develop new prescription algorithms for prosthetic ankle-foot devices to improve the current clinical practice guidelines. This information will lead to clinical prescriptions that facilitate the achievement of maximal functional ability and user satisfaction for individuals with lower limb loss. Specifically, this study will help to determine the appropriate functional and biomechanical measures to support the prescription of prosthetic ankle-foot devices; correlate patient goals and subjective measures with objective data to determine the optimal prosthetic ankle-foot category to facilitate the greatest overall function for the user; and finally, develop the criteria for the appropriate prescription of nonarticulating ESR, ART, and powered plantarflexion ESR ankle-foot devices.

VA and the DoD have historically been leaders in the early adoption of advanced prosthetic technology for the clinical care of veterans and service members with limb loss. Despite the recent (and ongoing) evolution of lower limb prosthetic technology and the large number of commercially available devices, there are limited guidelines to aid the limb loss care team in prescribing appropriate prosthetic technology to achieve optimal functional ability. With the expectation of continued active lifestyles for veterans and service members with limb loss, the absence of effective, evidence-based interventions not only limits near-term outcomes but likely also increases the susceptibility for secondary physical conditions and degenerative changes over the long term. Furthermore, projected trends indicate that the overall number of amputations will increase dramatically, largely attributable to the aging population and the number of people living with dysvascular disease and diabetes [4]. As the aging veteran population advances in these diseases, this will become a major quality-of-life concern for VA, and effective outcome-based clinical practice will be necessary to decrease long-term disability and provide high quality of life. Therefore, it is the goal of this proposal to develop evidence-based lower limb prosthetic prescription guidelines for the achievement of maximal functional ability and patient satisfaction. Following the completion of this research project, the biomechanical, functional, and subjective parameters that are the most indicative in yielding the most successful and appropriate ankle-foot device prescription will have been determined. Thus, the evidence-based outcomes obtained from this research investigation can be appropriately translated into clinical practice and drive the future of clinical care and research. As future technology develops and becomes available, this protocol will help to establish the methodological framework necessary to aid in the appropriate clinical prescription of prosthetic ankle-foot devices.

### Dissemination Plan

It is expected that the outcomes and results of this investigation can become an influential source of evidence-based health care practice for prosthetic prescription that can also be incorporated in lower extremity clinical practice guidelines. Disseminating the results of this study within the DoD, VA, and civilian health care systems will be critical in changing clinical practice to affect the quality of life of individuals with transtibial limb loss. First, both VA and the DoD are integrated networks that leverage various modalities to enable the dissemination and adoption of best practices among different disciplines. Specifically for limb loss care teams, the DoD and VA Extremity Trauma and Amputation Center of Excellence leads efforts to enhance the health care of veterans and service members. Participation in the Extremity Trauma and Amputation Center of Excellence webinar series will be an excellent opportunity to present the results of this study. The webinars reach a multidisciplinary group of clinicians, scientists, researchers, and other members of the limb loss care team. This webinar series contains presentations that are broadcast and available across the entire DoD and VA health care network and occurs every other month. This forum provides an excellent platform to present the results of this study to a large, diverse audience of researchers and health care professionals in the field of limb loss care. By disseminating our results to leaders and clinicians in the field of limb loss care, we can directly influence the care provided to veterans and service members with limb loss.

To reach stakeholders in the civilian health care systems, we aim to communicate the importance of the results of this study through leading peer-reviewed publications in scientific journals and presentations at professional conferences that target clinical providers (eg, Gait and Clinical Movement Analysis Society conference, American Society of Biomechanics conference, and Military Health System Research Symposium) and by sharing our data through large data repositories.

Finally, in addition to providing a wide distribution of results through peer-reviewed publications, outcomes will be disseminated to industry leaders for improvement of their products. The DoD and VA have supported similar efforts across the prosthetics industry. Specific, relevant results provided to industry leaders can help in the evolution of lower extremity prosthetic components, which will then lead to improved devices for veterans and service members.

